# Preoperative dexamethasone administration in hepatectomy of 25-min intermittent Pringle’s maneuver for hepatocellular carcinoma: protocol for a randomized controlled trial

**DOI:** 10.1186/s13063-023-07820-0

**Published:** 2023-11-30

**Keywords:** Dexamethasone, Hepatocellular carcinoma, Ischemia-reperfusion injury, Hepatectomy, Perioperative outcome

## Abstract

**Background:**

Our previous randomized controlled trial (RCT) have demonstrated that intermittent Pringle’s maneuver (IPM) with a 25-min ischemic interval can be applied safely and efficiently in open or laparoscopic hepatectomy in patients with hepatocellular carcinoma (HCC) patients. But prolonging the hepatic inflow blocking time will inevitably aggravate the ischemia-reperfusion injury (IRI) caused by systemic response. This RCT aims to evaluate the effect of administration of dexamethasone versus placebo before clamping the hilar pedicle on postoperative liver function, inflammatory response, and perioperative outcomes among HCC patients undergoing liver resection with 25-min hepatic inflow occlusion.

**Methods and analysis:**

This will be a randomized, dual-arm, parallel-group, double-blinded trial. All eligible and consecutive patients are coming from a regional medical center who are diagnosed with HCC and underwent radical R0/R1 resection. All participates are randomly allocated in dexamethasone group or placebo group. All surgeons, anesthesiologists, and outcome assessors will be blinded to allocation status. Primary endpoints are transaminase-based postoperative hepatic injury on seven consecutive days after surgery and assessed by their peak values as well as area under the curve (AUC) of the postoperative course of aminotransferases. Secondary endpoints are postoperative total bilirubin (TBil), coagulation function, inflammatory cytokines and their respective peaks, intraoperative blood loss, postoperative hospital stay, morbidity, and mortality. The above parameters will be compared using the corresponding statistical approach. Subgroup analysis will be performed according to the liver cirrhosis and major hepatectomy.

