### Outcome measures

All blood samples will be collected on PODs 1, 2, 3, 4, 5, 6, and 7 following the same procedure for performing serial laboratory evaluation. All blood samples will be collected at 7 a.m. every day, which then will be sent by the outcome assessor to the Department of Experimental Medicine for examining by a fixed physician. Preoperative laboratory parameters are viewed as baseline of postoperative laboratory parameters (if the postoperative stay is not more than 7 days, outcome assessors will be responsible for the subjects for blood sample collection).

Primary outcomes are as follows: peaks value of ALT and AST and AUC of ALT and AST.

Indicators of hepatocellular injury are as follows: ALT and AST of postoperative 7-day both the two groups; then, we will calculate the mean for postoperative 7-day after surgery to depict the line charts with mean ± stand error.

Peak values of ALT and AST as well as AUC values of the postoperative 7-day course of ALT and AST (peak value is defined as the maximum value measured in 7 days, and AUC is calculated by the value of postoperative 7 days). The magnitude of the effect of glucocorticoids on relieving surgical pressure and alleviating ischemia-reperfusion injury are assessed by the AUC surrounded by continuous ALT and AST, which is the metrics for declaring superiority of the tested intervention.

We decided that peaks value of ALT and AST and AUC of ALT and AST were primary outcomes after 16 July 2023.

Secondary outcomes:Intraoperative blood lossLiver function: assessed by measuring serum level of TBil and INR for coagulationInflammatory cytokines: assessed by IL-6, PCT, CRP, and their respective peaksPostoperative complications: according to the Clavien–Dindo grade, including major complications and minor complicationsPostoperative hospital staysMortality: defined as in-hospital death or death within 30 or 90 days after surgery

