### Statistical analysis

The trial is designed to test the superiority of dexamethasone to placebo with respect to the primary outcomes and secondary outcomes with the use of difference analysis. Superiority with respect to the primary outcomes are required before the secondary outcomes could be tested. All included participants will provide 80% power to detect superiority with respect to the primary outcomes. The AUC of ALT and AST will be tested for superiority, analyzed by Student’s *T* test or the Mann-Whitney *U* test.

Continuous variables will be presented as the mean ± standard deviation or median with its range based on normality testing and compared by an independent sample Student’s *T* test or the Mann-Whitney *U* test. Categorical variables will be presented as number (percentage) and compared using chi-square test or Fisher exact test. The modified intention-to-treat (ITT) principled analysis is applied for allocating patients into the group; moreover, when compliance is at a low level or the trial is no longer double-blinded, the as-treated (AT) analysis will be added to be supplements. Sensitivity analysis of missing data (loss to follow-up, death, withdrawal, etc.) will be conducted with the multiple-imputation approach. All tests for differences except primary outcomes are two-tailed and considered statistically significant if *P* values < 0.05. Bonferroni correction will be performed to correct for four primary outcomes statistically. We have changed the adjustment for multiple testing after 16 July 2023. All statistical analyses are performed by the SPSS version 20 and GraphPad Prism version 8.0.1.

As appropriate, the significance of postoperative categorical complications will be analyzed using chi-square test or Fisher exact test or will be tabulated and summarized using descriptive statistics.

Besides, according to the extent of resection and background of hepatic fibrosis after surgery, subgroup analysis will be performed to assess the protective effect of administration of dexamethasone before clamping the hilar pedicle on residual liver injury after undergoing liver resection with 25-min hepatic inflow occlusion.

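### The secondary laboratory markers are defined as postoperative levels in some sections and as peaks in another, and the one two-group test named fixes neither a single comparison per marker nor any use of the preoperative baseline

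*Protocol article*

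**What the plan says.** Five laboratory markers are secondary outcomes: TBil, INR, IL-6, PCT and CRP. Three sections describe them differently.

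- **Abstract (Methods and analysis):** "Secondary endpoints are postoperative total bilirubin (TBil), coagulation function, inflammatory cytokines and their respective peaks". These are postoperative values plus peaks, with no day or summary named. The sentence leaves open whether the peaks belong to all the markers or only to the cytokines.
- **Outcome measures:** the sampling rule reads "All blood samples will be collected on PODs 1, 2, 3, 4, 5, 6, and 7 following the same procedure for performing serial laboratory evaluation". TBil and INR enter as serum levels. IL-6, PCT and CRP enter as levels and also as peaks. The preoperative values are called the baseline.
- **Data collection:** the postoperative laboratory list has a peak for each of the five and no daily level or AUC for any of them. All five are also in the preoperative list.

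Statistical analysis says continuous variables are "compared by an independent sample Student’s *T* test or the Mann-Whitney *U* test". On error control it says "All tests for differences except primary outcomes are two-tailed and considered statistically significant if *P* values < 0.05", then "Bonferroni correction will be performed to correct for four primary outcomes statistically", and it sets a gate: "Superiority with respect to the primary outcomes are required before the secondary outcomes could be tested".

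**The concern.** A t or Mann-Whitney test takes one value per patient. For ALT and AST the protocol supplies such values by reducing the seven-day course to a peak and an AUC. For the secondary levels it supplies none beyond the peak, and it does not say that the peak replaces the level. An analyst could therefore test the peak, each day, a chosen day, or several of these, and each would fit the text.

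Two things are at stake. An isolated significant day could be reported as an effect on that marker, or the same marker could be called positive or negative depending on which version is reported. Also, the named test makes no use of the preoperative value, although the protocol collects it and designates it as the baseline.

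The opening matters more than usual here. Trial status gives unblinding on 16 July 2023, and the article says that the choice of primary outcomes and the multiplicity adjustment were settled after that date. A secondary definition that is still open can be settled with the results in view.

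**Working it through.** **Plan's own figure.** The protocol states no number of secondary tests and no error rate for them, so there is nothing to reproduce on this point. Its sample size does reproduce: 2 × (184.684 × (1.645 + 0.84) / 58.882)² = 121.5, so 122 per group, and 122 × 1.10 = 134.2, so 135. It rests on peak ALT and does not depend on the secondary markers.

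**Definitions side by side**

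| Marker | Abstract | Outcome measures | Data collection |
|---|---|---|---|
| TBil, INR | level, perhaps peak | level | peak |
| IL-6, PCT, CRP | level and peak | level and peak | peak |

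For TBil and INR, Outcome measures and Data collection name different quantities. For the other three, two sections name two quantities and one section names one.

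**Number of comparisons that fit the text**

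- Peak only: 5 tests.
- Every day: 5 markers × 7 days = 35 tests.
- Every day plus all five peaks: 35 + 5 = 40 tests.
- Every day plus only the three peaks in Outcome measures: 35 + 3 = 38 tests.

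**Expected false positives at 0.05 each, if no marker is affected and testing goes ahead**

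- 5 tests: 5 × 0.05 = 0.25
- 35 tests: 35 × 0.05 = 1.75
- 40 tests: 40 × 0.05 = 2.0

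**Chance of at least one false positive within one marker over seven daily tests.** With independent days this is 1 − 0.95⁷ = 0.30. Days in the same patient are correlated and the protocol gives no correlation, so it is assumed here as AR(1). Simulation with 20,000 null replicates per setting gave:

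| Assumed day-to-day correlation | Any false positive, one marker |
|---|---|
| 0.3 | 29% |
| 0.5 | 27% |
| 0.7 | 22% |
| 0.9 | 14% |

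A single comparison per marker gives 5%. Pooled over all 35 daily tests, the figure runs from 82% (correlation 0.3, markers independent) down to 51% (correlation 0.9, between-marker correlation 0.3). That pooled figure mixes in how alpha is shared between markers, which is a separate matter. Even five single tests give 1 − 0.95⁵ = 22.6% if independent.

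**What the gate does.** With four one-sided primary tests at 0.05/4 = 0.0125 each, the chance of passing the gate when dexamethasone has no effect on any outcome is at most 4 × 0.0125 = 5%. The chance of any secondary false positive is then no higher. If transaminases truly improve but a given secondary marker does not, the gate opens and the per-marker figures above apply in full.

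**Choice of summary.** Suppose one day has 60% power, so the standardised effect is 1.960 + 0.253 = 2.213. The SE of a seven-day mean relative to one day is √((1 + 6r)/7), which is 0.76 at r = 0.5 and 0.91 at r = 0.8 (equal correlation r assumed).

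- Same effect on all seven days: 2.213/0.91 = 2.43 and 2.213/0.76 = 2.93, giving power of 68% to 83%.
- Effect on only two of seven days (assumed): multiply by 2/7, giving 0.69 and 0.84, and power of about 10% to 13%.

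An average therefore gains for a sustained effect and loses heavily for a brief one.

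**The case against.** A reader might infer that the plan commits the trial to 40 day-wise tests. The documents do not support that. No section states a test for each day. The only stated use of daily values is, for ALT and AST, to "depict the line charts with mean ± stand error". The count of 40 is also 35 daily tests plus 5 peaks, not 40 daily tests. A two-group test on each patient's peak is valid, has no within-patient dependence, needs five tests and agrees with Data collection. All of this stands.

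A reader might also take about two false positives as expected if the drug does nothing. The gate rules that out, since it is passed at most about 5% of the time in that case. This stands too. It leaves uncovered the case where the primaries succeed, which is when the secondary markers would be reported.

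An unadjusted comparison in a randomised trial is unbiased, so ignoring the baseline costs precision, not validity. Missed draws are partly covered by the arrangement for sampling patients with short stays and by the multiple-imputation sensitivity analysis. Nor is a seven-day-average mixed model plainly better: its advantage assumes a constant effect, while the intervention is a single dose before clamping.

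Finally, the article is condensed, and a repeated-measures model could properly sit in an analysis plan that is not shown. Its absence is therefore not the point. The point is that sections of this article define the same endpoints differently, while Statistical analysis fixes a test that does not settle the difference.

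**Conclusion.** The point holds as an inconsistency of definition joined to a test that leaves the number of comparisons per marker open. The wording permits anything from 5 comparisons to 35 daily plus 5 peak comparisons, each at unadjusted two-sided 0.05.

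If daily testing were done for a marker that dexamethasone does not affect, and the gate had been passed, the chance of a false claim for that marker would be 14-29% instead of 5%. That range rests on assumed AR(1) correlations of 0.9 to 0.3. These are consequences of a permitted reading, not of a declared plan. Leaving the baseline value out of the comparison is a loss of precision whose size cannot be given, because the protocol reports no correlation between preoperative and postoperative values.

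Only the interpretation of secondary laboratory outcomes is affected. The sample size and the primary analysis are not.

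**What to change.** 1. Use one definition for TBil, INR, IL-6, PCT and CRP in the abstract, Data collection and Outcome measures, with one summary per marker. The peak is the smallest change, because Data collection already lists it for all five. A seven-day AUC or average, in line with the AUC used for ALT and AST, is the alternative.
2. In Statistical analysis, compare that summary once per marker in a linear model with arm and the preoperative value, on the log scale where the marker is skewed. Report the estimate with its confidence interval.
3. Show daily values with confidence intervals as descriptive only, without day-wise P values.
4. Date the change and state that it was made after the unblinding of 16 July 2023.

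The cost is wording and a simple model in software already named (SPSS), with no new data. Day-specific significance claims are given up, and a short-lived effect may be diluted if an average is chosen. Disclosure does not make the choice prespecified, so the secondary results need to be read with that in mind. The five remaining tests stay unadjusted against each other unless that is addressed separately.

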**Discussion:**

Based on our previous study, we will explore further the effect of glucocorticoid administration on attenuating the surgical stress response in order to follow securely 25-min hepatic inflow occlusion. Therefore, the trial protocol is reasonable and the results of the trial may be clinically significant.

**Trial registration:**

This trial was registered on 3 December 2022, in the Chinese Clinical Trial Registry (http://www.chictr.org.cn), ChiCTR2200066381. The protocol version is V1.0 (20221104).

**Supplementary Information:**

The online version contains supplementary material available at 10.1186/s13063-023-07820-0.

## Background

At present, the control of intraoperative bleeding is still a crucial topic in hepatectomy. Specialists have tested various methods in attempts to decrease blood loss, transfusion requirements, and morbidity during hepatectomy [1]. The IPM is one of the most common methods of vascular control strategies which is a cycle of 15-min inflow occlusion followed by 5-min reperfusion [2, 3]. One major concern of applying the IPM is IRI to the remnant liver [4, 5]. Although 15-min inflow occlusion has been considered a standard time for IPM [6], the optimal occlusion and reperfusion time to balance blood loss and IRI is pending. There are four RCTs comparing the perioperative outcome with prolonged IPM time versus standard 15-min IPM time [7–10]. Maartje et al. [7], Esaki et al. [8], and Kim et al. [9] reported that 30-min IPM induced the hepatocellular injury, and inflammatory responses are similar to that in 15-min IPM in patients who underwent liver resection, but their studies are limited to the case selection or sample size. One of them is our research, which demonstrates that IRI caused by 25-min IPM is not inferior to the 15-min IPM with a large sample of HCC patients and 25-min IPM is related to lower blood loss and higher speed for parenchyma transection [10]. We choose 25 min as the ischemic interval, because in East Asia, most HCC patients are accompanied with varying degrees of cirrhosis and liver function impairment.

Glucocorticoids, such as methylprednisolone, hydrocortisone, and dexamethasone, are proved to be effective drugs that modulate level of inflammatory cytokines and attenuate IRI stress [11]. But there are currently no international guidelines recommending the routine use of glucocorticoids when clamping the hepatic hilum during hepatectomy. In a systematic review of steroids in liver resection published in 2014 [12], Richardson et al. reported five RCTs. There was a total of 379 patients, with 190 patients in the pre-operative steroid group and 189 in the placebo group. The sample size was 33, 53, 73, 20, and 200, respectively. More than half of the patients came from one study from Japan. All five studies referred to post-operative complications, length of stay, post-operative serum total bilirubin (TBil), and serum prothrombin time (PT). There was a statistically significant reduction in post-operative TBil associated with the use of steroids [*P* = 0.05, OR: − 0.43, 95% confidence interval (CI): − 1.04 to − 0.015]. Data were available in four of the studies pertaining to post-operative serum interleukin-6 (IL-6). There was a significant reduction in serum IL-6 in association with steroid administration (*P* = 0.01, OR: − 46.4, 95% CI: − 83.4 to − 9.39). What is more, in the past two decades, RCTs of preoperative administration of glucocorticoids in patients undergoing liver resection have demonstrated favorable postoperative changes in systemic inflammation, including interleukin-10 (IL-10), tumor necrosis factor-α (TNF-α), C reactive protein (CRP), and liver function parameters, such as aspartate amine transferase (AST), alanine amine transferase (ALT), and PT [13–18]. Moreover, perioperative glucocorticoids administration can decrease the incidence of postoperative complications [13, 17].

Although the above studies have demonstrated that preoperative glucocorticoids administration may improve perioperative outcome for patients undergoing liver resection, evidence supporting improved postoperative outcome of prolonging the ischemic interval time in HCC patients with cirrhosis is lacking. Therefore, we design the trial to evaluate the effect of dexamethasone versus placebo on postoperative short-term outcome in HCC patients undergoing liver resection with 25-min IPM. Meanwhile, we will explore the effect of dexamethasone on HCC patients with cirrhosis.

## Methods and analysis

### Study design

This is a single-center, parallel, double-blinded, randomized controlled trial. Liver function, inflammatory cytokines, and perioperative outcomes will be compared between two groups (intravenous 10 mg dexamethasone versus equivalent saline) before 10 min of hepatic inflow occlusion to evaluate the effect of dexamethasone in HCC patients undergoing liver resection with 25-min IPM. All participants will be blinded to the grouping. This study will be conducted in accordance with the principles of the Declaration of Helsinki and conform to the “Standard Protocol Items: Recommendations for Interventional Trials” checklist [19].

### Study setting

This trial will be conducted at West China Hospital of Sichuan University in Chengdu, Sichuan, China. West China Hospital of Sichuan University is one of the largest regional medical centers in China, which performs more than 2000 liver resections for HCC per year. The Department of Liver Surgery is national key specialty, which is staffed by seven well-trained liver surgeons with over 20-year experience in liver surgery, four of whom will participate in the study. The investigators in the trial are responsible for completing the operation, managing and interpreting of the data, and writing of the final report and have the decision to submit the report for publication and have ultimate authority over any of these activities.

### Recruitment

This recruitment will be conducted from 3 December 2022 to 1 April 2023. A total of 270 consecutive patients who are eligible for the inclusion and exclusion criteria will be enrolled in this study. When physicians preliminarily evaluate the patient diagnosed with HCC at the outpatient clinic to be able to treat surgically, a trained research assistant will inform patient about the purpose, content, and points for attention of the trial; voluntariness; benefits and risks related to the study; principles of data protection and handling; and dissemination plans for the trial results. Then, the patient and/or immediate family may express their willingness to participate and sign the written informed consent of entering the trial. After enrollment in the cohort, all participates will provide consents for surgical treatments of the HCC, for entering a cohort randomly to receive a trial intervention, and for collecting and analyzing clinical, survival, and relevant medical data at each stage for the trial. Except for scientific research and communication with authorities in potential safety and regulatory issues, these consents have no plans for other purposes. Figure 1 and Table 1 present the study procedure and schedule for outcome assessment for the RCT.

**Fig. 1 Fig1:**
[figure not shown]
Flowchart of the study protocol. HCC, hepatocellular carcinoma; IPM, intermittent Pringle’s maneuver; ALT, alanine amine transferase; AUC, area under the curve; AST, aspartate amine transferase; TBil, total bilirubin; INR, international normalized ratio; IL-6, interleukin-6; PCT, procalcitonin; CRP, C reactive protein

**Table 1 Tab1:**
[figure not shown]
Schedule of enrollment, interventions, and assessments in the RCT

“×” indicates at which point of the RCT the respective assessments will take place

*RCT* randomized controlled trial, *ALT* alanine amine transferase, *AST* aspartate amine transferase, *AUC* area under the curve, *TBil* total bilirubin, *INR* international normalized ratio, *IL-6* interleukin-6, *PCT* procalcitonin, *CRP* C-reactive protein

### Inclusion criteria

All patients scheduled to undergo liver resection for HCC are considered as potential participants. Inclusion criteria are as follows: (1) IPM ischemic interval ≥ 25 min; (2) adequate functional reserves of important organ systems, New York Heart Association (NYHA) class I or II; pulmonary function is normal, mild, or moderate damage; chronic kidney disease (CKD) stage 1, 2, or 3; (3) normal liver function or well-reserved function before operation (Child–Pugh classes A or B with the score ≤ 7), (4) no other treatments for HCC before enrollment, such as portal vein embolization, transarterial chemoembolization, radiotherapy, targeted therapy, or immunotherapy.

